
**Fig. 1 Fig1:**
[figure not shown]
Study design of FIND’EM, a stepped wedge cluster randomised trial. Bars indicate the various time points at which the indicated number of blood collection clusters shifted from current practice (control) to ferritin-guided donation intervals (intervention) during the implementation period of the policy. The vertical arrows indicate the three measurement time points. **a** Planned timing of implementation. **b** Real timing of implementation

### Study population

Both new (i.e. a donor undergoing pre-donation screening) and repeat donors (i.e. a donor making a whole blood donation or attempt) are eligible to participate in this study. The intervention likely results in delayed effects. Ferritin levels of a donor visiting a blood collection centre where the intervention has been implemented will only be measured every fifth donation. Furthermore, the extension of donation intervals makes it necessary to allow the blood collection centres to be exposed to the intervention for a certain amount of time before donors return and the effectiveness of the new policy becomes observable. We therefore selected three measurement time points: (1) before implementation (i.e. baseline), (2) mid-implementation (when 55% of blood collection centres had implemented the policy) and (3) after complete implementation of ferritin-guided donation intervals. As Sanquin had already started the implementation of the ferritin-guided donation intervals in November 2017, before approval from the Ethical Advisory Board for the FIND’EM study, we were unable to collect questionnaire data from donors at baseline. However, baseline data on other outcomes (Hb and ferritin levels, low-Hb deferral and donor return) are measured after ethical approval in stored samples, and a large majority of the donors (99%) provide their consent to the routine request to ‘make the unusable remainder of my donation available for medical scientific research in general’ (Fig. 2). Whole blood donors who visit one of the 50 fixed blood collection centres during a pre-selected week at mid-implementation or after complete implementation are asked to participate by completing questionnaires. This makes the current study an open cohort design study with repeated cross-sectional measures and new samples at each measurement. Donors registering at the registration desk of one of the collection centres during one of these time points will receive a leaflet with information on why this study is performed, explaining that upon participation, the donor is asked to fill in a questionnaire and participation is voluntary, the leaflet contains contact details of the research team in case of any questions and a link to the study website with additional information and frequently asked questions. The donor is asked to read the study information while waiting for their health check. After the check, the donors will be asked whether they have read the study information. If the donor decides to participate, an informed consent form will be signed and the donor physician or nurse will sign the form as a representative of the researcher. Donors who decide not to participate are asked to write down the reason for non-participation.

**Fig. 2 Fig2:**
[figure not shown]
Spirit figure, schedule of intervention enrolment and assessments

### Control condition

Before each whole blood donation, a donor is seen by one of the doctors or nurses to check haemoglobin levels and blood pressure and screen for any indications a donor might not be eligible to donate whole blood at that moment. Sanquin’s current guidelines include Hb cut-offs for donor eligibility of > 13.5 g/dL for men and > 12.5 g/dL for women, which is in accordance with the international guidelines and European legislation [15]. Donors with low Hb (measured prior to donating in capillary blood with HemoCue 201, Angelholm, Sweden) are deferred from donating for 3 months.

### Intervention: ferritin-guided donation intervals

The ‘intervention’ includes ferritin-guided donation intervals with ferritin measurements in whole blood donors at pre-donation screening and every 5th donation, in addition to the standard Hb measurement as described as the control condition. Ferritin level cut-offs are based on the definitions for iron deficiency (< 15 ng/mL) and reduced iron level (≤ 30 ng/mL) by Alvarez-Ossorio et al. [12]. With respect to the duration of donation intervals, it is acknowledged that iron-deficient donors may need tailored donation intervals but knowledge on optimal recovery times for iron-deficient donors is lacking. Our deferral period is based on the study by Schotten et al. in which recovery of ferritin levels in new and repeat male donors was suggested to require donation intervals of 180 days [5]. If ferritin during the pre-donation screening is higher than 30 ng/mL, the donor is allowed to donate following regular donation schedules. If ferritin is ≤ 30 ng/mL but ≥ 15 ng/mL, the donor is allowed to donate during the next visit to the blood collection centre, but ferritin will be measured again from the blood sample taken during their first whole blood donation. If ferritin during pre-donation screening is < 15 ng/mL, the donor is not allowed to donate for 12 months. After 12 months, the donor is allowed to donate but ferritin is measured again from the blood sample taken during their first whole blood donation. If the donor experiences complaints that can be associated with a low ferritin level, the new donor is advised to visit his/her general practitioner (Fig. 3).

**Fig. 3 Fig3:**
[figure not shown]
Schematic of the standard operating procedure for ferritin-guided donation intervals. Asterisk indicates that if ferritin levels were ≤ 30 ng/mL previously, ferritin levels will be measured again after 6 or 12 months deferral before the donor is allowed to donate. Deferral strategies from this ferritin screening will follow the standard operating procedure of ‘repeat donor’

For repeat whole blood donors, the intervention includes ferritin measurements from blood samples taken at every fifth donation. When ferritin is > 30 ng/mL, donors are eligible to donate at normal donation intervals. If ferritin is ≤ 30 ng/mL but ≥ 15 ng/mL, donors are deferred for 6 months (Fig. 3). If ferritin is < 15 ng/mL, donors are deferred from donating for 12 months (Fig. 3). After deferral, ferritin levels are re-measured from blood taken during the next donation. When ferritin is < 30 ng/mL again, the ferritin level is re-measured after 6 or 12 months deferral, before the donor is allowed to donate. The deferral policy after this re-measured ferritin level follows that of repeat whole blood donors (Fig. 3). In addition, the donor may be advised to visit his/her general practitioner and/or to donate at a lower donation frequency. This decision is made by a donor physician, based on the donor’s medical history and coinciding iron deficiency-related complaints.

### Data collection

Pseudonymized data on age, sex, Hb levels and deferrals will be extracted from the donor database (eProgesa software application; MAK-SYSTEM) for all new and repeat whole blood donors who visit a fixed blood collection centre during a pre-selected week at one of the three measurement time points and gave consent for their information and left-over material to be used for research purposes. Furthermore, we will calculate donor return rates as the percentage of donors with a donation attempt within 6 months after the next allowed donation date. We will use stored plasma samples of new donors and repeat donors who made a donation attempt at one of the fixed blood collection centres during one of the pre-selected measurement time points to determine ferritin levels in intervention and control groups. Ferritin will be measured on the Architect i2000sr (Abbott Diagnostics) from donation samples collected in K3EDTA tubes (Greiner) and stored at − 30 °C. After storage, ferritin levels may be lower than those in fresh samples [16]. Within the FIND’EM study, we will compare ferritin levels of donors donating at centres where the ferritin-guided donation interval policy was implemented to ferritin levels of donors donating at centres where the policy was not implemented yet. For both groups, we will use samples that were stored for the same time period. Therefore, we expect similar decreases of ferritin levels as a result of storage in both groups, still allowing this comparison. For the validation of ferritin levels from stored samples of donors participating in the FIND’EM study, we will compare ferritin levels from stored samples with ferritin levels measured in fresh samples as part of the ferritin-guided donation interval policy.

At mid-implementation and after full implementation, all new and repeat whole blood donors who visit fixed blood collection centres during the pre-selected week are asked to participate in additional data collection for this study and to fill in an informed consent form. Subsequently, donors are asked to complete often-used or validated questionnaires during or right after whole blood donation. These questionnaires assess physical and mental wellbeing (SF-36 questionnaire [17]), fatigue (Checklist Individual Strength) [18], donation-related symptoms [19], restless legs syndrome and pica [8], cognitive functioning (Cognitive Failure Questionnaire; supplementary file) and warm glow [20]. Questionnaires are completed online, using Qualtrics XM®, and are accessible by following a hyperlink or using the provided QR code. If donors are unable to fill in the questionnaires online, the blood collection staff provides paper questionnaires or questionnaires are sent by (e-)mail.

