### Study design

The FIND’EM study is a stepped wedge cluster randomised trial involving whole blood donors from all 50 fixed blood collection centres in the Netherlands. The stepped wedge cluster randomised design is increasingly being used in the evaluation of ‘service delivery type interventions’, which are bounded by logistical or policy constraints. A stepped wedge design is a one-way crossover trial in which several allocation groups start at different time points with the implementation of the new policy [14]. For FIND’EM, this involves random and sequential crossover of clusters from the current policy without ferritin measurements to the policy including ferritin-guided donation intervals, until all clusters are exposed to this new policy (Fig. 1). The numbers 1 to 29 have been randomly assigned to one of the 29 blood collection clusters. Allowing only a maximum of two clusters of a similar topographic region to each implementation step, the two clusters with the lowest numbers from each region were allocated to step 1, the clusters with the third and fourth lowest numbers from each region were allocated to step 2, the clusters with the fifth and sixth lowest numbers from each region were allocated to step 3 and the remaining clusters were allocated to step 4. The allocation was not concealed and the planned timing of crossover of all blood collection clusters was revealed before the start of the implementation period. In November 2017, Sanquin started with implementing ferritin-guided donation intervals in eight clusters of blood collection centres (28% of all blood collection centres). The next three implementation steps were planned for May 2018, October 2018 and February 2019. The number of repeat whole blood donors with low ferritin levels appeared to be higher than anticipated. Therefore, to ensure sufficient blood supply in The Netherlands, further implementation had to be delayed and executed in smaller steps. The second step of implementation thus included four clusters of collection centres from different topographic regions (step 2a), instead of the planned eight clusters, and was scheduled for May 2018. The remaining clusters of step two implemented ferritin-guided donation intervals in October 2018 (step 2b). The third step was again split into two implementation waves, in which four clusters implemented the policy in March 2019 (step 3a) and three additional clusters of step 3 started in October 2019 (step 3b). Due to logistical reasons, one cluster randomised to step 3 was not able to implement the ferritin-guided donation intervals in October 2019. The fourth and final step included the remaining six clusters of collection centres and was executed in November 2019 (Fig. 1). On average, a total of 1275 whole blood donations are done at collection centres of each implementation step per week. Effectively, this stepwise strategy results in a gradual increase of the intervention group and a simultaneously decreasing control group. This implementation strategy and the ferritin-guided donation interval policy itself was approved by Sanquin’s Board of Directors after review and approval by Sanquin’s Medical and Ethical Advisory Boards. Additionally, Sanquin’s Ethical Advisory Board has approved the FIND’EM protocol for additional questionnaires and ferritin measurements. As part of standard practice, blood donors are asked for consent for their unusable remainder of the donation to be used for medical scientific research. Consent for the use of this material was included in the ethical approval for the current study. All research activities commenced after ethical approval was obtained. All participating donors who filled in a questionnaire provided additional written informed consent. As the FIND’EM study is a minimal risk study, a data monitoring committee is not needed.

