### Data analyses

Descriptive statistics will be provided for the donor population at baseline, mid-implementation and after full implementation. Linear mixed models (i.e., multilevel analysis) will be used to investigate differences in Hb and ferritin levels, low-Hb deferral, donor return rates and donor health between intervention and control groups using data collected at baseline, mid-implementation and after implementation. Two-level models with donors nested within blood collection clusters will be fitted, with a random intercept for cluster to adjust for the correlation between measurements of donors within the same cluster. All models include a binary variable indicating whether the observation was done before or after the start of the intervention and will be adjusted for the time point of implementation of the policy (fixed variable, time in months since the start of implementation period). Because of the nature of our outcome measures and because we include a new sample of donors at every measurement time point, we do not expect robust methods to be appropriate for sensitivity analyses. To investigate how the impact of ferritin-guided donation intervals develops over time, the latter will also be included as an effect modifier [14]. An intention-to-treat approach will be used and stratified analyses will be performed to investigate differences in the effectiveness of ferritin-guided donation intervals for male and female donors.

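### Outcomes are measured only in donors who attend, and the policy keeps repeat donors who test low away for 6 or 12 months, so attendee ferritin rises even if no donor's iron changes

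*Protocol article*

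**What the plan says.** **Who is measured.** The Data collection section extracts age, sex, Hb and deferrals "for all new and repeat whole blood donors who visit a fixed blood collection centre during a pre-selected week" at one of three time points. Ferritin comes from "stored plasma samples of new donors and repeat donors who made a donation attempt" in the same windows. The contrast is stated openly: "we will compare ferritin levels of donors donating at centres where the ferritin-guided donation interval policy was implemented", against donors at centres that have not yet switched. Questionnaires are offered to the same week's visitors. The Study population section describes a new cross-section at each time point.

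**What the policy does.** In the Intervention section, a repeat donor is tested at every fifth donation. At 15 to 30 ng/mL, "donors are deferred for 6 months"; below 15 ng/mL, "donors are deferred from donating for 12 months". The control condition has a 3-month low-Hb deferral but no ferritin deferral.

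**How it is analysed.** Data analyses plans a mixed model with a policy indicator, time and a random cluster intercept. It adds that "An intention-to-treat approach will be used".

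**What is acknowledged.** Study population and Discussion treat longer intervals only as a reason for delayed effects. The Discussion covers recruitment bias for questionnaires and says that all available data from consenting donors are used for the other outcomes. Absence through deferral is not mentioned.

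**The concern.** The policy acts on ferritin, and it acts by keeping low-ferritin repeat donors away from the place where ferritin is then measured. Under control those donors can attend and be counted. Under the intervention some of them are absent in the sampled week because they tested low. The groups then differ in composition as well as in any real iron recovery. A model with policy, time and cluster terms attributes both to the policy.

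The removal is unlikely to be negligible. Study design reports: "The number of repeat whole blood donors with low ferritin levels appeared to be higher than anticipated", to the point that rollout was slowed to protect the blood supply.

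At stake is the conclusion. The Abstract says the trial will show whether the policy reduces iron deficiency and improves donor health. A higher mean among attendees cannot show that for the donor population if part of it comes from the absence of deferred donors.

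**Working it through.** **1. Planning inputs.** Sample size calculations gives a difference of 4 ng/mL, SD 54, two-sided 5% and 80% power.

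- Per group: 2 × (1.96 + 0.8416)² × 54² / 4² = 2861. The total is 5722, against 5720 stated.
- Centres by the printed formula: 5720 / (1 + 149 × 0.9) = 42.3, against 42 stated.

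The figures reproduce, so 4 ng/mL is the yardstick. The clustering formula is a separate matter and is not judged here.

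**2. Who can be missing from an intervention week.**

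| Donor | Can the policy remove the donor from the sampled week? |
|---|---|
| New donor at screening | No; sampled before the policy acts |
| New donor, 15–30 ng/mL | Not deferred; may donate at the next visit |
| New donor, < 15 ng/mL | Screening visit is counted; absent for 12 months afterwards |
| Repeat donor, not yet at a fifth donation | No |
| Repeat donor tested at 15–30 ng/mL | Yes, 6 months |
| Repeat donor tested at < 15 ng/mL | Yes, 12 months |

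**3. Size with every ferritin value held fixed.** Let M be the mean among would-be attendees, p the share at or below 30 ng/mL, m the mean of that share, and f the fraction of that share absent through deferral. Then

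rise in attendee mean = f·p·(M − m) / (1 − f·p).

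This is positive for any distribution with donors on both sides of the cut-off, because m is then below M. For a size, assume lognormal ferritin with SD 54. The article gives no mean, so M is varied. Example, M = 50: p = 0.444 and m = 17.3.

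- f = 20%: 0.0888 × 32.7 / 0.911 = 3.2 ng/mL.
- f = 30%: 0.133 × 32.7 / 0.867 = 5.0 ng/mL.

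| Assumed mean | p | Rise, f = 20% | Rise, f = 30% | f that gives 4 ng/mL |
|---|---|---|---|---|
| 40 | 0.59 | 3.4 | 5.5 | 23% |
| 50 | 0.44 | 3.2 | 5.0 | 25% |
| 60 | 0.30 | 2.6 | 4.0 | 30% |
| 70 | 0.19 | 1.9 | 2.8 | 41% |
| 80 | 0.10 | 1.1 | 1.7 | 67% |

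With a gamma distribution, the f that gives 4 ng/mL is 19%, 23% and 40% at means of 40, 60 and 80.

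**4. Effect of the testing schedule.** A simulation kept each donor's ferritin constant, tested at every fifth donation, applied the 6- or 12-month deferral and re-tested at the next donation. Means were 40, 60 and 80, and mean visit intervals 120 to 240 days. The rise in attendee mean was near 0 one month after switching, about 0.6 to 4.0 ng/mL at 6 months, 0.2 to 9.6 at 12 months and 1.2 to 11.4 at about 16 months. It covers repeat donors only and does not model within-donor fluctuation, which would weaken the selection.

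**5. Exposure in this trial.** Eight clusters switched in November 2017, four in May 2018 and four in October 2018: 16 of 29, or 55%, which matches the stated mid-implementation share. Four more followed in March 2019. If the mid-implementation week fell between those last two dates, the first eight clusters had been exposed for 11 to 16 months. At the final measurement (planned for the end of November 2019), the three October 2019 and six November 2019 clusters, 9 of 29, had been exposed for two months at most and would show little thinning.

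**The case against.** **The attendee contrast is stated openly.** The article says it compares donors who donate under each policy. That is a legitimate service-level quantity, and low-Hb deferral is naturally counted per attempt. Analysing clusters by policy status in repeated cross-sections is also a recognisable use of intention-to-treat. This stands as a description of attendees. It does not make the attendees comparable, and it does not carry the conclusion about donors' iron.

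**The thinning is partial.** A reader might infer that every intervention donor at or below 30 ng/mL is missing. The text does not support that: see the table in the working. Women may donate at most 3 times a year, so five donations take at least 5/3 years, about 20 months. Control clusters also lose some low-iron donors through low-Hb deferral. All of this stands and limits the size.

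**The size is assumed.** Neither the mean nor the share absent is given. At a mean of 80, a lognormal needs 67% absent to reach 4 ng/mL. This stands.

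**The planning effect.** It is tempting to say that the 4 ng/mL itself is a removal effect, since it was seen over 6 months, no longer than the shortest deferral. The article does not say whether it is a cross-sectional or a within-donor change. If it is within-donor, the argument does not apply.

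**Donor return.** A reader might call the definition, "the percentage of donors with a donation attempt within 6 months after the next allowed donation date", biased because the policy moves that date. It gives every donor the same 6 months of eligible time, which is defensible. No direction of bias has been shown.

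**Sensitivity analyses may sit in an unseen analysis plan.** That could supply a correction. It would not change what this article fixes: the sampled population and the intended conclusion.

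**Conclusion.** The concern holds for ferritin in repeat donors. Attendance in the sampled week is affected by the policy, the planned model does not correct for it, and the bias is upward. With an assumed lognormal distribution, SD 54 and mean 40 to 80 ng/mL, absence of 20 to 30% of donors at or below 30 ng/mL adds about 1 to 5.5 ng/mL with no change in any donor. That can be comparable to the 4 ng/mL target, but the documents do not fix the true size.

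For Hb, low-Hb deferral and questionnaires, a bias in the same favourable direction is plausible, because the Introduction links depleted iron to donor health and to low-Hb deferral. It is not quantified, and the same section says Hb does not reflect iron status.

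None of this shows that the policy has no real effect. Returning donors may have recovered, and the observed difference would then mix recovery with selection. The plan as written cannot separate the two.

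**What to change.** 1. **Wording.** Limit the attendee-only result to donors presenting to donate. Do not conclude from it alone that iron deficiency fell or health improved in the donor population.
2. **Report the absence.** By cluster and time point, give the share of active repeat donors who are in ferritin deferral.
3. **Pre-specified sensitivity analysis.** Define the donor population identically in both conditions, for example registered active repeat donors per cluster.
   - Count deferred donors with a weight equal to their expected chance of attending in the sampled week, given their earlier donation frequency. Adding each at full weight would be wrong: at maximum frequency a man attends about one week in 10 (52/5) and a woman one in 17 (52/3), so deferred donors would be over-weighted at least 10- to 17-fold.
   - Use each deferred donor's last policy ferritin, converted with the planned fresh-versus-stored validation, since stored values may be lower.
   - Give two bounds: no recovery, and recovery as seen in returning deferred donors.
4. **Low-Hb deferral.** Report it also per registered active donor over a fixed calendar window.
5. **Donor return.** Keep the stated definition. A common window from the index visit, long enough for the longest deferral plus 6 months (18 months), may be added only as a supplementary measure. It gives undeferred donors about 14 to 16 months of eligibility against 6 for a donor deferred for 12 months.

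The cost is one extra database extraction, the added analysis and some rewording. No new samples are needed. The headline effect may become smaller.

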The use of a stepped wedge cluster randomised trial approach allows to implement and simultaneously evaluate the policy. As data collection takes place at multiple time points during the implementation period, all blood collection centres contribute data under both the control and intervention condition. Furthermore, this design makes it possible to investigate the effects as if it was a randomised controlled trial by correcting for time and clustering of donors and blood collection centres. This design also introduces some challenges, including prolonged trial duration compared to a standard randomised controlled trial, time-varying confounding, instructing all parties involved, making sure each cluster is committed and performing the assigned policy, and communication with whole blood donors [14, 21]. Furthermore, the lack of blinding to the allocation for both participants and trial staff may introduce a risk of bias [22]. Recruitment bias for the questionnaire data is limited by inviting all eligible donors at the different measurement time points to participate. For other outcomes, all available information from donors who gave consent for their unusable remainder of the donation to be used for medical scientific research was used in the current study. Detection bias is expected to be minimal because outcome assessment does not include any judgement from the researchers [22]. For our sample size calculation, we considered multiple clustering effects that may be present in our study design. An individual autocorrelation coefficient will not affect our sample size as there are no repeated measurements from the same participants. As participants in the same cluster are more alike than participants in another cluster, we included an intraclass correlation coefficient of 0.10. Finally, it may be necessary to take into account a cluster autocorrelation coefficient. However, the cluster autocorrelation coefficient may be difficult to determine and the impact on the total sample size is probably limited [23]. Although the appropriate sample size calculation for stepped wedge designs is still subject of discussion, it is a potential limitation that we did not take into account a cluster autocorrelation coefficient in our sample size calculation. The setting of Sanquin as one organisation with multiple blood collection centres has some advantages in the execution of a stepped wedge cluster randomised trial compared to locally organised general practices or hospitals, for example. The blood collection centres are randomised to implementation steps and instructed to perform the assigned policy, with centralised organisation and monitoring. To our knowledge, this method has never been used in transfusion-related research. The effectiveness of the ferritin-guided donation interval policy on Hb and ferritin levels, Hb deferral rates, donor return rates and donor health likely has a delayed response, because (1) donors’ ferritin levels are only measured when they make a fifth donation and (2) the policy involves donation interval extension which delays follow-up. Delaying the implementation period of ferritin-guided donation intervals should therefore have minimal negative impact on the outcome of the study. Sanquin’s Ethical Advisory board approved the FIND’EM study protocol after the start of the implementation period and we were therefore not able to collect baseline questionnaire data in September 2017. Furthermore, this together with logistic constraints made it impossible to collect data at each implementation step. Therefore, we might have less detailed data on the effects of the new policy on the outcomes over time compared to a design with outcome measurements at each cross-over period. The secondary outcome donor health is measured at mid-implementation and after complete implementation. Investigating the effectiveness of the ferritin-guided donation intervals policy on donor health is limited to the use of questionnaire data collected at mid-implementation and after the implementation period. Data on ferritin levels is available at baseline, mid-implementation and after complete implementation of the policy.

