## Trial status

At the time of manuscript submission, all clusters have implemented the ferritin-guided donation interval policy. Data collection at mid-implementation has been completed and data collection after completion of the implementation is planned for the end of November 2019. Ferritin measurements from stored blood samples are scheduled for 2020. The research team will communicate the results of the FIND’EM study via a final report without publication restrictions.

Protocol version 3, June 16, 2020

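### Control and intervention ferritin samples share a storage time only within a measurement wave, so the comparison depends on a time term that the plan words in two ways

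*Protocol article*

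**What the plan says.** **Storage (Data collection).** The article concedes the problem: "After storage, ferritin levels may be lower than those in fresh samples". It then sets it aside: "For both groups, we will use samples that were stored for the same time period", and so "we expect similar decreases of ferritin levels as a result of storage in both groups, still allowing this comparison". A validation is added: "we will compare ferritin levels from stored samples with ferritin levels measured in fresh samples as part of the ferritin-guided donation interval policy".

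**Timing.** Study population lists a baseline time point before implementation and two later ones: "2) mid-implementation (when 55% of blood collection centres had implemented the policy) and (3) after complete implementation of ferritin-guided donation intervals". The Discussion dates the baseline: "we were therefore not able to collect baseline questionnaire data in September 2017". Under Study design, the first clusters cross over in November 2017 and the last in November 2019. Trial status places the final data collection at the end of November 2019 and adds: "Ferritin measurements from stored blood samples are scheduled for 2020".

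**Model (Data analyses).** Data from all three time points are pooled in a mixed model with a random intercept for cluster and a binary intervention indicator, "adjusted for the time point of implementation of the policy (fixed variable, time in months since the start of implementation period").

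**The concern.** The equal-storage statement is the plan's stated reason for comparing stored ferritin between the groups. The timeline contradicts it for the pooled comparison that Data analyses specifies. Only the mid-implementation wave contains both conditions. Baseline samples are the oldest and are all control; post samples are the youngest and are all intervention. If older samples read lower, as the plan says they may, control ferritin is lowered by more than intervention ferritin.

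The time term must then carry the whole adjustment. Its description joins two different variables. One is the point at which the policy was implemented, which is a fixed attribute of a cluster. The other is months counted from a single study-wide start, which is calendar time. The first does not adjust for differences between waves; the second does so at least in part. At stake is the estimate for ferritin, the outcome on which the trial was sized, where the difference sought is only 4 ng/mL.

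**Working it through.** **1. The plan's yardstick.** Sample size calculations uses a difference of 4 ng/mL, SD 54, two-sided 5% and 80% power. Total N = 2 × 2 × (54/4)² × (1.960 + 0.842)² ≈ 5722, against the stated 5720, so it is reproduced. What follows does not depend on it beyond the use of 4 ng/mL as a scale.

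**2. Who is control, and when.** Crossovers from Study design: 8 clusters in November 2017 (month 0), 4 in May 2018 (month 6), 4 in October 2018 (month 11), 4 in March 2019 (month 16), 3 in October 2019 (month 23) and 6 in November 2019 (month 24). The total is 29. The stated 55% at mid-implementation is 16/29, which holds from October 2018 until the March 2019 step. The exact mid date is not given.

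| Wave | Control clusters | Intervention clusters | Months stored if assayed in June 2020 (assumed) |
|---|---|---|---|
| Baseline, September 2017 | 29 | 0 | 33 |
| Mid, October 2018 to March 2019 | 13 | 16 | 20 to 15 |
| Post, end of November 2019 | 0 | 29 | 7 |

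Of the control cluster-waves, 29/42 = 69% are baseline. Of the intervention cluster-waves, 29/45 = 64% are post. Neither set has a concurrent comparator.

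**3. Storage gap**, with equal numbers per cluster-wave:
- Mid wave stored 20 months: control (29×33 + 13×20)/42 = 29.0; intervention (16×20 + 29×7)/45 = 11.6; gap 17.4 months.
- Mid wave stored 15 months: control (29×33 + 13×15)/42 = 27.4; intervention (16×15 + 29×7)/45 = 9.8; gap 17.6 months.

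Any common assay date gives the same gap. For assay dates that differ within 2020, baseline samples are still at least 28 − 13 = 15 months older than post samples (baseline assayed in January, post in December).

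**4. How much of a shift between waves enters the effect.** The model is y = μ + θ·(intervention) + time term + cluster intercept + error. The generalised least squares estimate of θ is a weighted sum of the 87 cluster-wave means, and summing the weights by wave shows what a shift common to a wave contributes. Inputs from the article: 29 clusters, 7500/29 ≈ 259 donors per cluster-wave, intraclass correlation 0.1, SD 54. Hence the between-cluster variance is 0.1 × 54² = 291.6, and the residual variance of a cluster-wave mean is 0.9 × 54²/259 ≈ 10.1. Baseline is at month −2, post at month 24.5, and mid is varied over months 11 to 15.

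| Time term | Weight: baseline | Weight: mid | Weight: post | SE (ng/mL) |
|---|---|---|---|---|
| Cluster's crossover month | −0.78 | +0.05 | +0.72 | 0.72 |
| Calendar month, linear, mid at month 11 | −0.12 | +0.24 | −0.12 | 1.44 |
| Calendar month, linear, mid at month 13 | +0.03 | −0.06 | +0.03 | 1.45 |
| Calendar month, linear, mid at month 15 | +0.12 | −0.34 | +0.22 | 1.43 |
| Wave as a category | 0 | 0 | 0 | 1.45 |

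**5. In ng/mL.** The size of the storage loss is not in the documents. Let L be an assumed amount by which baseline reads lower than post.
- *Crossover month.* With mid halfway, false effect = 0.776 L − 0.052 L/2 = 0.75 L, i.e. 0.75, 1.5 and 3.0 ng/mL for L = 1, 2 and 4. Moving the mid wave between the two extremes changes the factor only from 0.72 to 0.78. The sign favours the policy.
- *Linear calendar month.* A linear drift is removed exactly. A departure d of the mid wave from the straight line contributes d × (mid weight). With L = 4 and the mid wave reading exactly like baseline, mid at month 15: the line at mid is −4 + 4 × 17/26.5 = −1.43, d = −2.57, false effect = +0.9. With mid reading like post: d = +1.43, false effect = −0.5. At month 11 the same two extremes give −0.5 and +0.5.
- *Wave as a category.* Zero for any L and any shape.

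Any other shift between waves, such as a secular trend, acts in the same way.

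**The case against.** The strongest reply is that the time term most naturally means calendar time. The bracket counts from the start of the implementation period, and there is only one such start. The same section uses this term as an effect modifier to see how the impact develops, which fits calendar time better than a date fixed within each cluster. The Discussion names time-varying confounding and speaks of correcting for time. On that reading the bias is small, has no fixed sign and vanishes near month 12 to 13. This stands, and it means that the 75% figure describes one possible reading and not the expected analysis.

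It can also be said that linear or categorical coding is ordinarily settled in an analysis plan, and that the article never says linear. That is fair, and the coding alone would not be a finding. What remains is a stated reason that the timeline contradicts and a covariate described as two different things.

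A reader might infer that the three waves differ in season. The documents do not establish this: with a mid wave in October or November 2018, all three would fall between September and November. A reader might also infer that the validation is useless. That goes too far. Fresh values exist for policy donors at both mid and post, at two storage durations, so they carry some information on loss over time. Baseline samples, however, predate any ferritin measurement under the policy. Reaching them needs extrapolation to longer storage, not a direct check.

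**Conclusion.** The statement that both groups' samples were stored equally long is correct only within a measurement wave. For the pooled comparison, control samples are about 17 to 18 months older on average, assuming one assay date and equal numbers per cluster-wave. Whether this reaches the estimate depends on a term that the plan words in two ways. Under the crossover-month reading about three quarters of any baseline-to-post shift enters. Under linear calendar time only curvature enters, with a weight of about +0.24 to −0.34 for a mid date between months 11 and 15.

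A reader might conclude that the trial will report storage loss as a policy effect. The documents do not support that. The calendar reading is the likelier one, and no size for the storage loss is given; 1 to 4 ng/mL is an assumed range. The weights rest on the article's own intraclass correlation of 0.1, SD of 54 and about 7500 donors per wave. At an intraclass correlation of 0.01 the crossover-month factor is still about 0.75.

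**What to change.** - **Data collection:** limit the equal-storage statement to samples within each measurement time point.
- **Data analyses:** define the time term as measurement wave, fitted as a categorical fixed effect. Use three levels for ferritin, Hb, low-Hb deferral and donor return, and two for donor health, which has no baseline wave.
- **Data collection:** state that no fresh policy ferritin exists for baseline samples, so the comparison of fresh with stored values cannot validate them directly.

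Keep ferritin on the ng/mL scale of the sample size; a log transformation is not part of this change.

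The cost is one model term and two sentences, with no new data. The standard error is about 1.45 ng/mL, essentially that of linear calendar time (1.43 to 1.45). It is double the 0.72 of the crossover-month model, but that figure is too small because the model ignores differences between waves. With 1.45, power for 4 ng/mL under the article's inputs is Φ(4/1.453 − 1.96) = Φ(0.79) ≈ 79%, close to the planned 80%.
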